All ipsilateral iliac arterial lesions should be treated with angioplasty and/or stenting concomitantly and residual stenosis should be less than 50%. Treatment of tibioperoneal lesions is recommended only in cases of critical limb ischemia. There should exist at least one patent (<50% stenosis) tibioperoneal run-off vessel with good antegrade flow.

A final angiography will be performed after the intervention in both groups, with the use of the same angles and magnifications used in the baseline angiograms. Simultaneously, reference vessel diameter (RVD), minimal luminal diameter (MLD), percent diameter stenosis, and acute gain should be measured. The reference vessel diameter will be obtained from averaging 5-mm segments proximal and distal to the lesion. Technical success will be defined as the successful access and deployment of the stent and less than 30% diameter residual stenosis after the revascularization.

For the post-procedural medication, aspirin 100 mg and clopidogrel 75 mg will be administered once daily for one month. Then, patients of each group will be randomized by web-based randomization to receive either clopidogrel 75 mg or cilostazol 100 mg once daily in addition to aspirin 100 mg for at least 11 months in a 1:1 manner.

After enrollment and index procedure, clinical follow-up will be planned at 1, 6, and 12 months to evaluate clinical outcomes and ankle-brachial index score. Also, all patients will be recommended to have a follow-up catheter angiography or duplex ultrasound at 12 months according to local clinical practice. The incidence of stent fracture and binary patency will be assessed by plain X-ray and quantitative femoral angiography. The investigators will be urged to follow up on patients, either by office visits or by telephone contacts, as necessary. Patient adherence to the study drug and side effects will be checked and monitored at every outpatient visit. The decision of drug discontinuation will be discussed and checked under the physician’s recommendation.

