### Statistical analysis

#### Sample size calculation

From previous studies, including ABSOLUTE [7], FAST [8], and ASTRON [9], recurrence rates in femoropopliteal lesions after one year were 32%, 34.4%, and 37%, respectively - approximately 35% on average. The recurrence rate for the SMART™ CONTROL stent was 34.8% in the SUPER-SL study - a multicenter, randomized controlled trial that compared two self-expanding nitinol stents, the SMART™ CONTROL and Luminexx stents, in femoropopliteal lesions [14]. So far, there are limited data on the one-year primary patency rate of the COMPLETE™-SE stent. Based on previous research results, the SMART™ CONTROL stent group will be the control group, and the COMPLETE™-SE stent group will be the experimental group. Based on the SUPER-SL results, the one-year primary patency of the SMART™ CONTROL stent is estimated to be 65% and the one-year primary patency of the COMPLETE™-SE stent is estimated to be 80%, which is higher than that of the SMART™ CONTROL stent. Recurrence will be defined as more than 50% restenosis or total occlusion under invasive angiography, or if invasive angiography is not performed, PSVR ≥2.5 when evaluated with duplex ultrasound. The statistical significance level is set at 5%, the power of test is set as 80%, and the randomization ratio is set as 1:1. Test for proportion and chi-square method are used. Using standard sample size formula, it was calculated that 138 patients per group are needed for a total of 346 patients, after accounting for a 20% dropout rate.

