### Statistical analysis

Categorical variables will be expressed as delivery rate when comparing baseline features between the SMART™ CONTROL and COMPLETE™-SE stent groups or the clopidogrel and cilostazol groups, and for categorical variables, comparisons between groups will use the chi-square or Fisher’s exact test. Continuous variables will be expressed as mean ± standard deviation, and for continuous variables, comparisons between groups will use the Student’s t-test. The primary and secondary endpoints will be analyzed using both intention-to-treat analysis (all subjects assigned to a treatment group) and per-protocol analysis (only subjects completed the treatment protocol). Study endpoints will also be analyzed per patient. For the primary endpoint (12-month binary restenosis rate) comparisons of the two patient groups will use the chi-square or Fisher’s exact test. At the end of the 12 months, cumulative restenosis rates will be calculated. All secondary endpoint analysis will be performed using the Student’s t-test, chi-square test, or Fisher’s exact test. Also, clinical outcomes such as revascularization of the target vessel, death, major cardiovascular events including myocardial infarction and cerebral infarction, and limb salvage rates will be analyzed using Kaplan-Meier survival estimates and a comparison of the groups will be performed using the log-rank test. A *P* value <0.05 is considered to be statistically significant. In order to evaluate the risk factors for recurrence, defined as restenosis or total occlusion, univariate and multivariate logistic regression analysis will be performed. Present research has concluded that there will be a very low chance of missing data to cause bias, and therefore, missing data for the major endpoints will be excluded from the analysis data. For repeated measurements for the secondary endpoints, last observation carried forward (LOCF) can be applied. The SPSS 20.0 (SPSS Inc, Chicago, Illinois, United States) statistics program will be used for all analysis.

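### Patients with a missing primary outcome are excluded on an unsupported no-bias premise, so the promised ITT analysis becomes a complete-case analysis, with a 20% dropout allowance and no stated sensitivity analysis

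*Protocol article*

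**What the plan says.** All of this is in the Protocol article.

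- **Analysis population** (Statistical analysis): primary and secondary endpoints get both a per-protocol analysis and an "intention-to-treat analysis (all subjects assigned to a treatment group".
- **Missing primary data** (same section): "missing data for the major endpoints will be excluded from the analysis data". The reason given is that "there will be a very low chance of missing data to cause bias". No figure, mechanism or sensitivity analysis accompanies it.
- **Repeated secondary measures** (same section): "For repeated measurements for the secondary endpoints, last observation carried forward (LOCF) can be applied".
- **Dropout** (Sample size calculation): "138 patients per group are needed for a total of 346 patients, after accounting for a 20% dropout rate".
- **Ascertainment** (Randomization and interventions): "all patients will be recommended to have a follow-up catheter angiography or duplex ultrasound at 12 months according to local clinical practice". Follow-up by telephone is also allowed where needed.
- **Endpoint** (Outcome measures): binary restenosis at 12 months by catheter angiography or duplex ultrasound. The article does not say how a reintervention, bypass, amputation or death before month 12 enters it.

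**The concern.** An analysis that drops every patient without a restenosis result is not an analysis of all subjects assigned. The article uses the intention-to-treat label and then fixes a rule that gives something else. What would have to hold the rule up is the no-bias premise, and that is only asserted.

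The rest of the article gives reason to doubt it. The trial is sized so that a fifth of patients can be lost. Month-12 imaging is a recommendation that follows local practice, so whether a patient is imaged may depend on symptoms. A telephone contact cannot give an angiogram or a velocity ratio. The population includes critical limb ischemia (Rutherford 4 to 6), in which amputation, bypass or death before imaging is foreseeable.

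The exclusion rule also touches known failures. The Appendix defines target lesion revascularization (TLR) as performed for restenosis. Read plainly, a patient with such a procedure at month 5 and no image at month 12 could be dropped although the failure is on record.

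At stake is the validity of the primary stent comparison. A larger sample would not cure it.

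**Working it through.** **1. The plan's own figure.** Inputs from Sample size calculation: restenosis 35% versus 20% (patency 65% and 80%), 5% significance (two-sided assumed; sidedness is not stated), 80% power, 1:1 allocation.

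n = [1.960 × √(2 × 0.275 × 0.725) + 0.842 × √(0.35 × 0.65 + 0.20 × 0.80)]² / 0.15² = 137.9, so 138 per arm. Then 138/0.8 = 172.5, so 173 per arm and 346 in total. Both figures reproduce. The allowance is 173 − 138 = 35 patients per arm. Power is 80.0% with 138 per arm and 88.1% with 173, so exclusion leaves the planned power intact. The problem is bias.

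**2. When exclusion biases the comparison.** All missingness patterns here are assumptions; the documents give none.

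- *Unrelated to restenosis:* no bias, type I error 5%.
- *Same dependence in both arms:* suppose 30% of restenosed and 10% of patent patients are lost in each arm. A true 35% is observed as 0.245/(0.245 + 0.585) = 29.5%, and a true 20% as 0.14/(0.14 + 0.72) = 16.3%. The odds ratio is 2.15 before and after, and equal true rates stay equal. The risk difference falls from 15 to 13.2 points.
- *Different dependence by arm, no true difference:* true rate 35% in both arms, 20% missing in each. The observed rate is 0.35 × (1 − r)/0.8, where r is the share of restenosed patients lost.

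| r, arm A | r, arm B | Observed A | Observed B | Type I error |
|---|---|---|---|---|
| 20% | 20% | 35.0% | 35.0% | 5% |
| 20% | 30% | 35.0% | 30.6% | about 12% |
| 20% | 40% | 35.0% | 26.3% | about 35% |

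**3. How far 35 missing per arm could move a positive result.** Assume the observed data match the design rates: 48/138 (SMART CONTROL) versus 28/138 (COMPLETE-SE). The difference is 14.5 points, p = 0.007. Now put all 173 per arm in the denominator (chi-square, no continuity correction).

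| Assumption for the 35 missing per arm | Restenosed, of 173 each | Difference (points) | p |
|---|---|---|---|
| All restenosed in both arms | 83 v 63 | 11.6 | 0.030 |
| 35% in both arms | 60 v 40 | 11.6 | 0.018 |
| SMART at observed rate (12), COMPLETE 15 of 35 | 60 v 43 | 9.8 | 0.046 |
| SMART at observed rate (12), COMPLETE 16 of 35 | 60 v 44 | 9.2 | 0.061 |
| No SMART, all COMPLETE | 48 v 63 | −8.7 | 0.08 |
| All SMART, no COMPLETE | 83 v 28 | +31.8 | <0.001 |

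The tipping point of 16/35 is 46%, against 20% (28/138) among observed COMPLETE-SE patients. The last two rows are extreme bounds, not plausible scenarios.

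**4. LOCF, secondary endpoints only.** The ABI is assessed at 1, 6 and 12 months. Assume an ABI of 0.90 in patent limbs, and in restenosed limbs 0.85 at 6 months and 0.65 at 12. With 35% versus 20% restenosis the true 12-month difference is (0.35 − 0.20) × 0.25 = 0.0375. A missing restenosed patient has 0.85 carried forward.

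- 30% of restenosed patients missing in the higher-rate arm, 10% in the other: (0.90 − 0.20 × 0.23) − (0.90 − 0.35 × 0.19) = 0.0205.
- The reverse: (0.90 − 0.20 × 0.19) − (0.90 − 0.35 × 0.23) = 0.0425.

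The difference can shrink or grow.

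**The case against.** Several points on the other side stand.

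- A reader might infer that the article says few data will be missing and so contradicts its own 20%. It says that missing data are unlikely to cause bias. The 20% is a planning allowance, not a forecast. It makes the premise need support but does not refute it.
- A reader might infer that the comparison is valid only if missingness is unrelated to restenosis. Step 2 shows otherwise: equal dependence in both arms preserves the type I error and the odds ratio. The type I error inflation in the table needs a mechanism that differs by arm, and the documents supply none.
- A reader might conclude that known failures will be deleted. The article does not say so. It mentions cumulative restenosis rates at 12 months without defining them, and it analyses revascularization, death and limb salvage by Kaplan-Meier. Those events stay visible in secondary analyses, and the full protocol may settle how they count.
- A reader might tie LOCF to the primary comparison or assume that it hides a stent effect. It is optional, limited to repeated secondary measures, and can bias either way.

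It could also be said that missing-data detail belongs in the analysis plan. That does not answer the point, because the article itself states the exclusion rule and its justification.

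**Conclusion.** The concern holds in this limited form. The article fixes exclusion of missing primary outcomes, supports it only with an assertion, and calls the analysis intention-to-treat although the resulting set is not all subjects assigned. With the plan's own allowance of about 35 of 173 patients per arm, exclusion can matter: a p = 0.007 result at the design rates is lost if 16 of 35 missing COMPLETE-SE patients are restenosed while missing SMART CONTROL patients follow their observed rate. That takes a rate among the missing more than double the observed one, so it measures fragility and does not predict the outcome.

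Neither the direction nor the size of any bias can be derived from the documents, and every missingness scenario above is an assumption. Loss of documented failures is a plausible reading, not stated text. LOCF is a separate and lesser matter for secondary endpoints. The sample size is correct and unaffected.

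**What to change.** For the primary endpoint:

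1. Make the primary analysis all randomized patients by assigned stent, with complete-case and per-protocol as sensitivity analyses under those names.
2. Count documented restenosis, occlusion, or TLR or bypass for restenosis before month 12 as restenosis. This settles the endpoint definition as well as the missing data, so it should be written in as such.
3. State how death and amputation before imaging are handled.
4. Multiply impute the remaining missing outcomes by stent arm, using the lesion-length stratum, antiplatelet arm, and the ABI and Rutherford data.
5. Add a tipping-point analysis that varies the imputed restenosis rate separately by arm.
6. Delete the sentence that claims little chance of bias.

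For repeated ABI, replace the optional LOCF with a likelihood-based mixed model for repeated measures.

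The cost is revised wording and some extra analysis programming, with no added patients or visits. The article reports recruitment as ongoing, so the change can still be specified before the data are analysed.

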### Trial organization

#### Executive committee

The Executive Committee will be composed of the study chairperson and selected members among the investigators. This committee is responsible for overseeing the administrative progress of the study and will approve the final trial design and protocol issued to the Data and Safety Monitoring Board (DSMB) and the clinical sites. This committee will also be responsible for reviewing the final results, determining the methods of presentation and publication, and selection of secondary projects and publications by members of the Steering Committee. The Executive Committee also holds the right to modify or stop the study prematurely based on recommendations from the DSMB.

### Data Safety Monitoring Board (DSMB)

The frequency of the DSMB meetings will be determined prior to study commencement. Additionally, the DSMB may call a meeting at any time if there is reason to suspect that safety is an issue. The DSMB is responsible for making recommendations regarding any safety or compliance issues throughout the course of the study and may recommend to the Executive Committee to modify or stop the study. However, all final decisions regarding study modifications rest with the Executive Committee.

All cumulative safety data will be reported to the DSMB and reviewed on an ongoing basis throughout enrollment and follow-up periods to ensure patient safety. Every effort will be made to allow the DSMB to conduct an unbiased review of patient safety information. All DSMB reports will be made available to the appropriate agencies upon request but will otherwise remain strictly confidential.

Prior to the DSMB’s first review of the data, the DSMB charter will be drafted. The DSMB will develop a consensus understanding of all trial endpoints and definitions used in the event adjudication process. All DSMB reports will remain strictly confidential, but will be made available to the regulatory body upon request.

### Clinical Event Adjudication Committee (CEAC)

The Clinical Events Committee (CEAC) is comprised of interventional and non-interventional cardiologists who are not involved in the study. The CEAC is charged with the development of specific criteria used for the categorization of clinical events and clinical endpoints in the study which are based on protocol. At the onset of the trial, the CEAC will establish explicit rules outlining the minimum amount of data required and the algorithm followed in order to classify a clinical event. All members of the CEAC will be blinded to the primary results of the trial. The CEAC will meet regularly to review and adjudicate all clinical events. The CEAC will also review and rule on all deaths that occur throughout the trial.

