### Outcome measures

The primary endpoint of this study is the rate of binary restenosis (stenosis of at least 50% of the luminal diameter) or PSVR (peak systolic velocity ratio) ≥2.5 or 0 (PSVR = peak systolic velocity within the area of stenosis divided by peak systolic velocity in a normal adjacent proximal artery segment) in the treated segment at 12 months after the intervention as determined by catheter angiography or duplex ultrasound. The secondary endpoints are as follows: 1) composite of binary restenosis and major stent fracture (moderate or severe stent fracture); 2) stent fracture rate according to fracture grade (minor, moderate, severe); 3) limb salvage rate free of above-the-ankle amputation; 4) sustained clinical improvement rate at 12-month follow-up; 5) repeated target lesion revascularization (TLR) rate; 6) repeated target extremity revascularization (TER) rate; 7) total reocclusion rate; 8) comparison of angiograph variables consisting of late loss and restenosis rate; 9) ankle-brachial index (ABI) at 12 months; 10) the rate of major adverse cardiovascular events (MACE) composed of all-cause death, myocardial infarction, repeat percutaneous coronary intervention (PCI), and stroke at 12 months; 11) incidence of geographic miss during stent deployment due to jumping and/or elongation; 12) rate of binary restenosis or PSVR ≥2.5 or 0 according to clopidogrel and cilostazol; and 13) major bleeding rate between clopidogrel and cilostazol group. The detailed definitions are summarized in the Appendix.

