## Appendix

### Endpoints definitions

Binary restenosis: defined as a reduction in the luminal diameter of >50% according to the worst angiographic view at the narrowest site within the treated segment plus the 10-mm segments proximal and distal to the treated segment by catheter angiography or PSVR ≥2.5 (PSVR = peak systolic velocity within the area of stenosis divided by peak systolic velocity in a normal adjacent proximal artery segment) or total occlusion by duplex ultrasound. Stent fracture rate according fracture grade (minor, moderate, severe) [12]: plain X-ray examinations for the stent fracture are used or performed using at least two different angulations (30 to 45° difference) and the highest available magnification. Stent fracture is classified as minor (single strut fracture), moderate (fracture of more than 2 struts), or severe (complete separation of stent segments). Target lesion revascularization (TLR): defined as any repeat percutaneous intervention of the target lesion or bypass surgery of the target vessel performed for restenosis because of a return of ischemic symptoms, decrease of at least 1 Rutherford category, decrease in the ankle brachial index of >0.15, or restenosis of >50% as measured by catheter angiography. The target lesion is defined as the treated segment from 10 mm proximal to the stent and to 10 mm distal to the stent. Target extremity revascularization (TER): defined as any repeat percutaneous intervention of the target extremity or bypass surgery of the target extremity performed for restenosis because of a return of ischemic symptoms, decrease of at least 1 Rutherford category, decrease in the ankle brachial index of >0.15, or restenosis of >50% as measured by catheter angiography. Limb salvage: defined as survival free of amputation. Amputation is defined as above-ankle amputation of the index limb. Sustained clinical improvement rate [36, 37]: defined as persistent ABI value ≥0.15 and persistent improvement of ≥1 class according to Rutherford throughout follow-up when compared with baseline without the need for repeat TLR in surviving patients. Late loss: defined as a change in MLD from final angiogram to follow-up. Major adverse cardiac events (MACE): defined as composite of all-cause death, myocardial infarction, cerebrovascular stroke, and target lesion revascularization.

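### The event committee is blinded to the trial's results, not to stent or antiplatelet assignment, which leaves the judgement-based secondary clinical endpoints (chiefly TLR and TER) without stated masking

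*Protocol article*

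**What the plan says.** In the Protocol article, the section on the Clinical Event Adjudication Committee (CEAC) states: "All members of the CEAC will be blinded to the primary results of the trial". The same section describes the members as "interventional and non-interventional cardiologists who are not involved in the study". On classification rules, to be fixed before events accrue, it says: "the CEAC will establish explicit rules outlining the minimum amount of data required and the algorithm followed in order to classify a clinical event". On the conduct of reviews it says: "The CEAC will meet regularly to review and adjudicate all clinical events". The committee also rules on every death.

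This is the only blinding statement about this trial. The word appears once more, in the rationale for the drug comparison, where it describes a cited trial of clopidogrel against aspirin. The section on randomization and interventions describes web-based 1:1 allocation to stent and, after a month of common treatment, web-based 1:1 allocation to drug. It mentions no placebo and no masking of operators or patients.

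The clinical events concerned are secondary endpoints. The Appendix definitions of TLR and TER require a repeat procedure "performed for restenosis because of a return of ischemic symptoms" or for one of the listed alternatives. The Appendix defines MACE as a "composite of all-cause death, myocardial infarction, cerebrovascular stroke, and target lesion revascularization". The last secondary endpoint in the Outcome measures section is the "major bleeding rate between clopidogrel and cilostazol group".

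**The concern.** Blinding of an event committee is meant to stop knowledge of the patient's treatment from influencing how that patient's event is classified. An adjudicator who has never seen the trial's results can still treat two similar events differently if the file shows the stent or the drug. The sentence therefore names a safeguard whose object does not serve its purpose.

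This matters because the trial is described with no other masking and has a directional hypothesis: the Discussion expects COMPLETE-SE to resist fracture or restenosis better. If adjudication leaned with that expectation, events would be lost or gained in one arm only, and the comparison of that endpoint would be biased. TLR also feeds other endpoints, so one call can count several times.

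**Working it through.** **1. What the stated blinding can conceal.** The primary result is a comparison of 12-month restenosis between arms. The committee reviews events at regular meetings during the trial. For much of that work the comparison does not yet exist, so being blind to it withholds nothing. Once it exists, hiding it still does not hide an individual's assignment. Nothing else in the article supplies that concealment.

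**2. Which endpoints are exposed.**

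| Endpoint | What has to be decided | Exposure |
|---|---|---|
| Primary: binary restenosis | Angiography or duplex reading; CEAC not described as the reader | Outside this point |
| TLR, TER | Whether the repeat procedure was for restenosis with returned symptoms, a Rutherford change, an ABI fall above 0.15, or angiographic restenosis above 50% | Main exposure: cause is attributed, though two alternatives are measured thresholds |
| MI, stroke | Classification of the event | Some |
| MACE (Appendix), sustained clinical improvement | Both definitions use TLR | Inherited from TLR |
| Major bleeding by drug | Haemoglobin or haematocrit fall, or intracranial haemorrhage | Small |
| All-cause death, above-ankle amputation | Occurrence | Small |

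MACE inherits TLR only under the Appendix definition. The Outcome measures section lists repeat coronary intervention in that place instead.

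**3. The plan's own figure.** Inputs from the sample size section: restenosis 35% and 20% (patency 65% and 80%), 5% significance, 80% power, 1:1 allocation, 20% dropout. Sidedness is not stated; two-sided is taken.

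n = [1.960·√(2·0.275·0.725) + 0.842·√(0.35·0.65 + 0.20·0.80)]² / 0.15² = 137.9, so 138 per group. Then 138/0.80 = 172.5, so 173 per arm and 346 in total. This reproduces the plan. The blinding point changes none of it; it only supplies the 173 used below.

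**4. Illustration of size.** None of the following inputs is in the documents: a true TLR rate of 15% in both arms, and knowledge of assignment causing a fraction f of true events to be dropped in one arm only.

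- Expected events per arm: 173 × 0.15 = 26.
- Shift in the affected arm: 0.15·f. For f = 10%, 2.6/173 = 1.5 points. For f = 20%, 5.2/173 = 3.0 points. For f = 30%, 0.15 × 0.30 = 4.5 points.
- Chance that the two-sided 5% test rejects although the true rates are equal, with p = 0.15, q = 0.15(1 − f), d = p − q, p̄ = (p + q)/2, se₀ = √(2p̄(1 − p̄)/173), se₁ = √((p(1 − p) + q(1 − q))/173):

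P(reject) = 1 − Φ((1.96·se₀ − d)/se₁) + Φ((−1.96·se₀ − d)/se₁)

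| f | Rate in affected arm | Shift | P(reject) |
|---|---|---|---|
| 0 | 15.0% | 0 | 5.0% |
| 10% | 13.5% | 1.5 points | 6.8% |
| 20% | 12.0% | 3.0 points | 12.9% |
| 30% | 10.5% | 4.5 points | 24.0% |

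Equal misclassification in both arms would leave the two rates equal and the false-positive rate at 5%. The harm comes only from error that differs by arm.

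**The case against.** The strongest reply is that this is a condensed article. A full protocol or committee charter, neither shown, may blind the committee to allocation, and the sentence may be a slip for treatment assignment. That is possible, and it limits the conclusion to what is stated. It does not remove the point: the article is not silent on the object of blinding, it names one that does not conceal assignment. If the charter is right, the sentence still needs correcting to agree with it.

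Several further objections stand and set the limits.

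- A reader might infer that adjudication is wholly unprotected. The text does not support that: members come from outside the study, and rules and an algorithm are set at the onset. These reduce bias without concealing the arm.
- A reader might infer that bleeding calls are exposed because some criteria turn on a prolonged stay. Those criteria cover bleeding linked to the catheterization visit up to discharge. As the randomization section describes it, drug allocation comes after one month, so for an ordinary index stay these calls precede it. The general definition is largely numeric.
- A reader might infer that operators pick the stent. They do not; a web-based program allocates it, and the physician's discretion concerns spot stenting or full coverage. What matters is that they know which stent was used.
- The treating physician's open-label decision to re-intervene may be a larger source of bias in TLR than its later classification, and committee masking does not change that decision.
- The stents differ visibly (4 against 6 bridges, 24 against 36 struts), so a promise of complete stent masking could not be kept where images must be reviewed.

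**Conclusion.** The point holds in limited form. The sentence on CEAC blinding should be changed because it does not conceal stent or drug assignment and nothing else stated in the article does. The consequence is confined to secondary clinical endpoints that require judgement, chiefly TLR and TER, then MI, stroke and the composites that use TLR. A reader might take this as a threat to the primary endpoint; the article does not describe the committee as reading the 12-month imaging, so that does not follow.

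The size cannot be determined from the documents. On the assumed 15% TLR rate and one-sided loss of 10% to 30% of events, the false-positive rate for that endpoint would be about 6.8% to 24.0% instead of 5%. Those figures show how the bias would act; they are not a forecast, and the lower end is modest for a secondary endpoint. This is a correction that should be made, not one on which the trial's main conclusion depends.

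**What to change.** Replace the sentence on CEAC blinding with:

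> CEAC members will be blinded to stent and antiplatelet assignment; the data coordination center will remove stent name, device labels and study drug from event files, images will be included only where the event definition needs them, and any unavoidable unblinding through images will be recorded.

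If a charter already says this, the change only brings the article into line with it. The cost is a small amount of redaction by existing coordination staff. No endpoint, sample size or aspect of patient care changes, and recruitment is stated to be ongoing, so the change can still take effect. The remaining weakness is incomplete stent masking where angiograms or X-rays have to be seen. Recording those cases shows how many adjudications were affected. Drug assignment and device names in text can be redacted regardless.
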